## Abstract

**Background:** Coronavirus disease 2019 (COVID-19) was declared a global pandemic in March 2020 by the World Health Organization (WHO). As of July 2, 2022, COVID-19 has caused more than 545 million infections and 6.3 million deaths worldwide, posing a significant threat to human health. Currently, there is still a lack of effective prevention and control strategies for the variation and transmission of SARS-CoV-2. Traditional Chinese medicine (TCM), which has a unique theoretical system, has treated various conditions for thousands of years. Importantly, recent studies have revealed that TCM contributed significantly to COVID-19. SanHanHuaShi (SHHS) granules, a Chinese herbal medicine, which has been included in Protocol for the Diagnosis and Treatment of Novel Coronavirus Disease 2019 (6th to 9th editions) issued by the National Health Commission of China and used to prevent and treat COVID-19 disease. A previous retrospective cohort study showed that SHHS could significantly reduce the severity of mild and moderate COVID-19. However, there is an absence of high-quality randomized controlled clinical studies to confirm the clinical effectiveness of SHHS. Therefore, a clinical study protocol and a statistical analysis plan were designed to investigate the efficacy and safety of SHHS for the prevention and treatment of COVID-19. This study will increase the integrity and data transparency of the clinical research process, which is of great significance for improving the practical application of SHHS granules in the future.

**Methods and analysis:** The study was designed as a 7-day, randomized, parallel controlled, open-label, noninferiority clinical trial of positive drugs. A total of 240 patients with mild and moderate COVID-19 will be enrolled and randomly assigned to receive SanHanHuaShi granules or LianHuaQingWen granules treatment in a 1:1 ratio. Disease classification, vital signs, SARS-CoV-2 nucleic acid testing, symptoms, medications, adverse events, and safety evaluations will be recorded at each visit. The primary outcome will be the clinical symptom recovery rate. Secondary outcomes will include the recovery time of clinical symptoms, negative conversion time of SARS-CoV-2 nucleic acid test negative conversion rate, hospitalization time, antipyretic time, rate of conversion to severe patients, and time and rate of single symptom recovery. Adverse incidents and safety assessments will be documented. All data will be analyzed using a predetermined statistical analysis plan, including our method for imputation of missing data, primary and secondary outcome analyses, and safety outcomes.

**Discussion:** The results of this study will provide robust evidence to confirm the effectiveness and safety of SHHS in the treatment of COVID-19.

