Through modern pharmaceutical technology, the Chinese medicine decoction is extracted, concentrated, dried and shaped into a granular formulation. The quality control analysis of SHHS granules utilizing HPLC is provided by Jiangsu Kanion Pharmaceutical Co., Ltd. The quality control data and preliminary identification of the main components are available in **Additional file 1**. The daily dosage of SHHS granules is as follows: Houpo (*Magnolia officinalis* Rehd.et Wils.): 3.13g (equally 15 g herb medicine, abbreviated as 15 g), Jiaobinglang (*Areca catechu* L.):1.88g (9g), Caoguo (*Amomum tsao-ko* Crevost et Lemaire): 9g (1.88g), Mahuang (*Ephedra sinica* Stapf):6g (1.25g), Kuxingren (*Prunus armeniaca* L.var.*ansu* Maxim.): 9g (1.88g), Qianghuo (*Notopterygium incisum* Ting ex H.T.Chang): 15g (3.13g), Shengjiang (*Zingiber officinale* Rosc*.*): 15g (3.13g), Guanghuoxiang (*Pogostemon cablin*(Blanco) Benth.): 15g (3.13g), Peilan (*Eupatorium fortunei* Turcz*.*): 9g (1.88g), Cangzhu (*Atractylodes chinensis*(DC.) Koidz.): 15g (3.13g), Fuling (*Poria cocos*(Schw.)Wolf): 45g (9.38g), Baizhu (*Atractylodes macrocephala* Koidz.**):** 30g (6.25g), Shigao (*Gypsum Fibrosum*): 15g (3.13g), Jiaoshanzha (*Crataegus pinnatifida* Bge.var.*major* N.E.Br.): 9g (1.88g), Jiaomaiya (*Hordeum vulgare* L.): 9g (1.88g), Jiaoshenqu (*Massa Medicata Fermentata*): 15g (3.13g), Dilong (*Pheretima aspergillum* (E.Perrier)): 15g (3.13g), Xuchangqing (*Cynanchum paniculatum*(Bge.)Kitag.): 15g (3.13g), Mianmaguanzhong (*Dryopteris crassirhizoma* Nakai), 9g (1.88g), Tinglizi (*Descurainia sophia*(L.)Webb.ex Prantl.):15g (3.13g).

A previous retrospective cohort study showed that SHHS could considerably reduce the incidence of mild and moderate COVID-19 turning into severe disease (Tian et al., 2020). Although this study suggests that SHHS can prevent and treat COVID-19, there are no further randomized controlled clinical trials to confirm this. Therefore, we hypothesized that SHHS plays a therapeutic role no less than LHQW in patients with mild and moderate COVID-19. Consequently, we designed a randomized, parallel-controlled, open-label clinical trial to demonstrate the efficacy and safety of SHHS in the treatment of COVID-19. The primary objective of this study research is to describe a precise clinical study protocol and a predetermined statistical analysis plan.

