## Methods

### Study design

This study is a randomized, active parallel-controlled, open-label, and non-inferior phase 2 clinical trial in patients with mild and moderate COVID-19. A total of 240 patients who tested positive for SARS-CoV-2 will be enrolled in this study. The patients will be divided into two randomized groups and treated with granules of either SanHanHuaShi or LianHuaQingWen for 7 days. The Standard Protocol Items: Recommendations for Interventional Trials (SPIRIT) guidelines will be followed (Chan et al., 2013). (**Additional file 2**). The study procedure is summarized in Figure 1. The details of the study schedule for enrollment, interventions, and assessments are presented in Table 1.

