### Sample size

The study hypothesis is SHHS group will be non-inferior to LHQW group. Clinicians and statisticians set the non-inferiority threshold at 10% and predicted that the recovery rate of clinical symptoms after 7 days of LHQW is about 87% and that of SHHS is 90% according to the literature reports on similar drugs. It is estimated that 94 patients for each group, ie. a total of 188 patients are needed to achieve the power of 80% at a one-sided statistically significant level of 0.025. Considering the possible dropout rate of 20%, 240 patients will be enrolled, that is 120 patients for each group.

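### A non-inferior result would support only a statement relative to LHQW, yet the article plans to read it as confirming that SHHS is effective

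*Protocol article*

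**What the plan says.** Three places in the protocol article state an absolute aim or conclusion:

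- Abstract, closing line: "The results of this study will provide robust evidence to confirm the effectiveness and safety of SHHS in the treatment of COVID-19".
- Introduction, last paragraph: a "clinical trial to demonstrate the efficacy and safety of SHHS in the treatment of COVID-19".
- Discussion: if non-inferiority can be declared, the effects of SHHS on symptom management (and on severe disease and further indications) count as confirmed. The next sentence adds that all this depends on future data from several sources, both randomised and observational.

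The design is relative. Patients are "randomly assigned to receive SanHanHuaShi granules or LianHuaQingWen granules treatment in a 1:1 ratio", in a "non-inferior phase 2 clinical trial in patients with mild and moderate COVID-19". No untreated or placebo arm is described. The hypothesis, in the Introduction and again under Sample size, is that SHHS does no worse than LHQW. On the margin, Sample size says "Clinicians and statisticians set the non-inferiority threshold at 10" percent and goes on that they "predicted that the recovery rate of clinical symptoms after 7 days of LHQW is about 87% and that of SHHS is 90" percent, "according to the literature reports on similar drugs". The Introduction says that several randomised LHQW trials exist and describes their findings qualitatively, without an effect size.

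**The concern.** A non-inferiority trial against an active comparator shows efficacy only indirectly. It bounds how far the new product may fall short of the comparator. To conclude that the new product beats no treatment, one must also know that the comparator beats no treatment by at least the margin, on the same endpoint and over the same period. The article does not show that second piece of information, yet it states the efficacy conclusion.

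If a positive trial is reported as the article describes, readers will take efficacy of SHHS as established, when what was tested is a maximum shortfall against LHQW. How often that conclusion would be wrong depends on a quantity the article does not give.

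**Working it through.** **Inputs from the article (Sample size).** LHQW recovery 0.87; SHHS recovery 0.90; margin 0.10; one-sided level 0.025; power 80%; 94 per arm before dropout, 120 per arm enrolled with 20% dropout allowed.

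**Input not in the article (assumption).** Let e be the LHQW effect on day-7 recovery over no treatment. It is varied from 0 to 10 points. The untreated rate is then 0.87 − e.

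**Step 1: reproduce the stated sample size.** With unpooled variance,

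n = [0.87 × 0.13 + 0.90 × 0.10] × (1.960 + 0.842)² / (0.03 + 0.10)² = 0.2031 × 7.849 / 0.0169 = 94.3 per arm.

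At 94 per arm, SE = √(0.2031/94) = 0.0465, and power = Φ(0.13/0.0465 − 1.96) = Φ(0.837) = 79.9%. For dropout, 188/0.8 = 235, which 240 covers. The sample-size arithmetic is sound.

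**Step 2: what non-inferiority implies.** Write pS and pL for the true day-7 recovery rates on SHHS and LHQW, and p0 for the untreated rate. A positive result supports pS > pL − 0.10. Efficacy means pS > p0 = pL − e. The first implies the second only if e ≥ 0.10. With LHQW at 87%, that means an untreated rate of 77% or less. The article neither states nor excludes this.

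**Step 3: chance that an inert SHHS passes.** An inert SHHS has pS = 0.87 − e. The rule used is that the lower 95% limit of SHHS minus LHQW lies above −10 points:

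P(pass) = Φ((0.10 − e)/SE − 1.96), SE = √{[0.87 × 0.13 + pS(1 − pS)]/n}.

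Example, e = 0.05 and n = 120: pS = 0.82, SE = √[(0.1131 + 0.1476)/120] = 0.0466, and P = Φ(0.05/0.0466 − 1.96) = Φ(−0.887) = 18.7%.

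| Assumed LHQW effect | Implied untreated rate | 120 per arm | 94 per arm |
|---|---|---|---|
| 10 points | 77% | 2.5% | 2.5% |
| 7 points | 80% | 9% | 8% |
| 5 points | 82% | 19% | 16% |
| 3 points | 84% | 34% | 28% |
| 0 points | 87% | 63% | 53% |

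**Step 4: check.** Exact binomial enumeration of the same Wald rule gives 2.7%, 20% and 64% at 120 per arm, and 2.7%, 16% and 54% at 94 per arm, for effects of 10, 5 and 0 points. This agrees with the table to within about 1 point.

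**Limits of the calculation.** It uses a Wald interval, because that reproduces the planned size, and it treats one analysis as decisive, although the article analyses the primary outcome on both the full analysis set and the per-protocol set.

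**The case against.** Several points on the other side are sound.

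- The Abstract sentence is a general closing line and does not mention a non-inferior result. Only the Discussion makes that link, so the point depends on the Discussion as well.
- The hypothesis is stated correctly, in relative terms, in the Introduction and under Sample size. Efficacy and safety is also common shorthand for an active-controlled comparison.
- The Discussion tempers its claim by pointing to future data. This softens the reading but does not remove it, and the Abstract and Introduction carry no such caveat.
- A condensed article may leave the derivation of the margin to the full protocol. The phrase about literature on similar drugs may be meant to cover the margin as well as the rates. A reader might infer that the margin was set by judgement alone, with no regard to an LHQW effect. The text supports only the statement that no such link is shown here.
- A reader might also infer that LHQW does little, that the margin is too wide, or that high recovery would occur in both arms whatever was given. The documents support none of these. They give no natural-course rate; 87% and 90% are predicted rates on treatment; and the Introduction reports randomised evidence of potential LHQW benefits. The 63% and 53% figures need LHQW to have no effect at all, which nothing in the article asserts.

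What survives is narrower. The article states an efficacy conclusion, and the design it shows does not carry that conclusion without one further figure.

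**Conclusion.** The point holds in limited form, at moderate severity. On the shown design, a positive trial supports a shortfall of at most 10 points against LHQW in day-7 symptom recovery. It would imply efficacy only if LHQW's own benefit on that endpoint is reliably at least 10 points.

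The chance that an inert SHHS would be declared non-inferior ranges from 2.5% (LHQW adds 10 points) through about 16–19% (5 points) to 53–63% (no effect). These figures assume LHQW recovery of 87%, between 94 and 120 evaluable patients per arm, and the decision rule in step 3. They show how strongly the efficacy conclusion depends on the missing figure; they do not estimate the actual risk. The sample size, margin and comparison are not shown to be wrong. The fault is in the conclusion drawn from them.

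**What to change.** In the Abstract, the last paragraph of the Introduction and the Discussion, word the objective and conclusion relative to LHQW. For example: *a positive result shows that the proportion of patients recovered from symptoms at day 7 on SHHS is not more than 10 percentage points below that on LHQW; it is not by itself evidence of efficacy over no treatment.*

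Keep efficacy wording only if a documented LHQW-versus-control effect on day-7 recovery is, at its lower confidence limit, at least 10 points. Cite that figure, with its interval, beside the margin under Sample size. The LHQW trials cited in the Introduction are the natural place to look, but whether they report this endpoint cannot be judged from the article.

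The rewording needs no extra patients, procedures or analyses. Its cost is a more modest claim. The efficacy option also needs a review of LHQW evidence, which may not yield the required figure.

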**Clinical Trial Registration:**
http://www.chictr.org.cn. Trial number: ChiCTR2200058080. Registered on 29 March 2022.

## Introduction

The extremely contagious coronavirus disease 2019 (COVID-19), caused by the severe acute respiratory syndrome coronavirus 2 (SARS-COV-2), has become a global public health concern. COVID-19 has a wide range of clinical manifestations, leading to dysfunction of multiple organs and systems throughout the body and even death (Harrison et al., 2020). The most common symptoms in COVID-19 patients include fever, cough, shortness of breath, fatigue, gastrointestinal problems, and taste and smell disorders (Wiersinga et al., 2020; To et al., 2021). Although people of all ages are vulnerable to infection with the highly transmissible SARS-COV-2, elderly patients or patients with comorbidities are more likely to develop severe or critical disease (Hu B et al., 2021). Therefore, early diagnosis and intervention are essential to control the onset and management of COVID-19. However, currently there is no specific drug with clear evidence of targeting SARS-CoV-2. Therefore, exploring effective prevention and control strategies or drugs against SARS-COV-2 remains an international concern.

The safety and effectiveness of traditional Chinese medicine (TCM) have been widely recognized and evaluated for thousands of years. In the early stages of the outbreak, TCM was incorporated into prevention and treatment strategies, and played an important role in the fight against COVID-19 not only in China but also internationally (Huang et al., 2020; Chu et al., 2021; Huang et al., 2021; Lyu et al., 2021; Wang and Yang, 2021). Owing to the synergistic effect of multiple components and multiple targets, Chinese herbal medicine has a comprehensive therapeutic effect in antiviral, anti-inflammatory, and immunomodulatory functions, thereby aiding in preventing and treating COVID-19 (Li P et al., 2021; Li BH et al., 2021; Ren et al., 2021). With the increase in the number of recovered patients from COVID-19, post-acute sequelae of SARS-CoV-2 infection (PASC) become an important public health problem that can have a long-term impact on pulmonary and multiple extrapulmonary tissues and organs (Wang and Yang, 1827). TCM has a potential advantage in preventing and improving PASC in patients with convalescent COVID-19 (Li et al., 2020; An et al., 2021; Chen et al., 2022).

“Three Chinese medicines and three Chinese recipes” have been included in the 2019 Protocol for Diagnosis and Treatment of Novel Coronavirus Disease 2019 issued by the National Health Commission (NHC) of China and are recommended for the treatment of COVID-19. Several clinical and mechanistic studies have shown that a variety of TCM herbal preparations have the potential to treat COVID-19 (Shen and Yin, 2021; Wu and Zhong, 2021; Yang et al., 2021). LianHuaQingWen (LHQW) capsules or granules have been approved by the NHC to treat COVID-19 and are used extensively worldwide. Multiple randomized controlled clinical trials and mechanistic studies have confirmed the potential advantages of LHQW in improving clinical symptoms and prognosis in patients with COVID-19 (Runfeng et al., 2020; Xiao et al., 2020; Hu K et al., 2021).

Similarly, the Hanshiyi formula recommended in the 2019 Protocol for the Diagnosis and Treatment of Novel Coronavirus Disease 2019 (6^th^ to 9^th^ editions) for patients with mild and moderate COVID-19 is also clinically effective prescription used in many regions of China. To further promote the study and utilize TCM against COVID-19, the Hanshiyi formula was produced as SanHanHuaShi (SHHS) granules after verification of the production process and improvement of quality standards by Jiangsu Kanion Pharmaceutical Co., Ltd. The composition and dosage of the SanHanHuaShi granules were the same as those of the Hanshiyi formula. SHHS is composed of 20 Chinese herbs, which play a role in releasing the exterior and dissipating cold, ventilating the lung and expelling pathogens, dispelling filth, and eliminating turbidity based on the theory of TCM (Han et al., 2020).

Through modern pharmaceutical technology, the Chinese medicine decoction is extracted, concentrated, dried and shaped into a granular formulation. The quality control analysis of SHHS granules utilizing HPLC is provided by Jiangsu Kanion Pharmaceutical Co., Ltd. The quality control data and preliminary identification of the main components are available in **Additional file 1**. The daily dosage of SHHS granules is as follows: Houpo (*Magnolia officinalis* Rehd.et Wils.): 3.13g (equally 15 g herb medicine, abbreviated as 15 g), Jiaobinglang (*Areca catechu* L.):1.88g (9g), Caoguo (*Amomum tsao-ko* Crevost et Lemaire): 9g (1.88g), Mahuang (*Ephedra sinica* Stapf):6g (1.25g), Kuxingren (*Prunus armeniaca* L.var.*ansu* Maxim.): 9g (1.88g), Qianghuo (*Notopterygium incisum* Ting ex H.T.Chang): 15g (3.13g), Shengjiang (*Zingiber officinale* Rosc*.*): 15g (3.13g), Guanghuoxiang (*Pogostemon cablin*(Blanco) Benth.): 15g (3.13g), Peilan (*Eupatorium fortunei* Turcz*.*): 9g (1.88g), Cangzhu (*Atractylodes chinensis*(DC.) Koidz.): 15g (3.13g), Fuling (*Poria cocos*(Schw.)Wolf): 45g (9.38g), Baizhu (*Atractylodes macrocephala* Koidz.**):** 30g (6.25g), Shigao (*Gypsum Fibrosum*): 15g (3.13g), Jiaoshanzha (*Crataegus pinnatifida* Bge.var.*major* N.E.Br.): 9g (1.88g), Jiaomaiya (*Hordeum vulgare* L.): 9g (1.88g), Jiaoshenqu (*Massa Medicata Fermentata*): 15g (3.13g), Dilong (*Pheretima aspergillum* (E.Perrier)): 15g (3.13g), Xuchangqing (*Cynanchum paniculatum*(Bge.)Kitag.): 15g (3.13g), Mianmaguanzhong (*Dryopteris crassirhizoma* Nakai), 9g (1.88g), Tinglizi (*Descurainia sophia*(L.)Webb.ex Prantl.):15g (3.13g).

A previous retrospective cohort study showed that SHHS could considerably reduce the incidence of mild and moderate COVID-19 turning into severe disease (Tian et al., 2020). Although this study suggests that SHHS can prevent and treat COVID-19, there are no further randomized controlled clinical trials to confirm this. Therefore, we hypothesized that SHHS plays a therapeutic role no less than LHQW in patients with mild and moderate COVID-19. Consequently, we designed a randomized, parallel-controlled, open-label clinical trial to demonstrate the efficacy and safety of SHHS in the treatment of COVID-19. The primary objective of this study research is to describe a precise clinical study protocol and a predetermined statistical analysis plan.

## Methods

### Study design

This study is a randomized, active parallel-controlled, open-label, and non-inferior phase 2 clinical trial in patients with mild and moderate COVID-19. A total of 240 patients who tested positive for SARS-CoV-2 will be enrolled in this study. The patients will be divided into two randomized groups and treated with granules of either SanHanHuaShi or LianHuaQingWen for 7 days. The Standard Protocol Items: Recommendations for Interventional Trials (SPIRIT) guidelines will be followed (Chan et al., 2013). (**Additional file 2**). The study procedure is summarized in Figure 1. The details of the study schedule for enrollment, interventions, and assessments are presented in Table 1.

**FIGURE 1 F1:**
[figure not shown]
Flow diagram of the study.

**TABLE 1 T1:** SPIRIT Schedule of enrollment, interventions and assessments.

Visit project	Study period									
	Screen period (baseline)	Allocation	Visit							
Time of visit (day)	-1	-1-0	1	2	3	4	5	6	7	8
1. Enrollment										
Eligibility screening	●									
Informed consent	●									
Demographic characteristics	●									
Diagnosis and medical history	●									
Comorbid conditions	●									
2. Interventions										
Random allocation		●								
Administration of study drugs			●	●	●	●	●	●	●	
3. Assessments										
Vital signs	●		●	●	●	●	●	●	●	●
Symptoms	●		●	●	●	●	●	●	●	●
Clinical assessment	●		●	●	●	●	●	●	●	●
Combined drugs	●		●	●	●	●	●	●	●	●
SARS-CoV-2 PCR testing	●		●	●	●	●	●	●	●	●
Adverse event monitoring**			●	●	●	●	●	●	●	●
4. Other work										
Distribute drugs			●	●	●	●	●	●	●	
Recover drugs										●
End of study summary										●

** Throughout the study, ongoing observations and recordings of when this occurred were made.

### Recruitment of participants

This study will include 240 patients who test positive for COVID-19. The patients will be recruited from the Affiliated Hospital of Changchun University of Traditional Chinese Medicine (Jilin province, China). Recruiting advertising will be displayed online and on hospital notice boards. It will contain the study objectives, drugs, medical examinations, and the study eligibility conditions and application method. The study is open to individuals who meet the eligibility criteria and agree to participate. To obtain consent from prospective patients, investigators must outline the study objectives, requirements, and interventions and guarantee their understanding. Two resident physicians will evaluate the patients, each of whom will verify the participants’ study eligibility. Demographic data and reasons for non-participation of ineligible patients will also be documented. The recruitment process started in March 2022 and will last until March 2024. Patients will not participate in study design, recruitment, research procedures, analysis, or dissemination of findings. Medical examinations, laboratory tests, and therapies are provided at no cost to participants, and research may not reimburse them.

